### Biological Measurements

#### Blood Samples

A trained phlebotomist collected fasting peripheral blood at each visit (baseline, week 2, week 4, and week 6). Blood was collected into 10-mL EDTA tubes (Becton, Dickinson and Company) for peripheral blood mononuclear cells (PBMCs) extraction, 2 EDTA tubes (4 mL each) to measure insulin, glucose, and alpha-1 acid glycoproteins levels, and 1 serum tube without clot activators (4 mL) to measure cytokine, MMP-9, lipid, and high-sensitivity C-reactive proteins concentrations. Blood samples collected in the EDTA tubes were kept in a chilled box with ice packs until processing. Blood samples collected in the serum tubes were kept at room temperature for 45 minutes to allow coagulation before processing. Vacutainers (excluding those for PBMC extraction) were centrifuged at 2200 *g* for 10 minutes at 4 ℃, and aliquots were stored at –80 ℃ until analysis.

The PBMCs were extracted using standard procedures (Multimedia Appendix 2) at the Department of Microbiology and Immunology, University of Otago, Dunedin, New Zealand, and Mātai Hāora-Centre for Redox Biology and Medicine laboratory at the University of Otago, Christchurch, New Zealand. The extracted cells were stored in liquid nitrogen until analyses at the Malaghan Institute of Medical Research (Wellington, New Zealand). Immuno-profiling of the PBMCs, including phenotypic and functional markers, will be performed using spectral flow cytometry.

Plasma cytokines including IL-1β, IL-6, IL-8, IL-10, IL-12p70, IL-17A, IL-18, IL-23, IL-33, interferon-α2, interferon-γ, TNF-α, and monocyte chemoattractant protein-1 will be measured using a cytokine bead assay (MILLIPLEX MAP Kit Human Cytokine Chemokine Magnetic Bead Panel Immunology Assay, Millipore) as per the manufacturer’s instructions at the Malaghan Institute of Medical Research (Wellington, New Zealand).

Plasma lipids, high-sensitivity C-reactive proteins, and insulin concentrations will be measured using enzymatic assays (Abbott C series analyzer, Abbott Diagnostics), immunoturbidimetric assay (Cobas c311 analyzer, Roche Diagnostics), and Cobas e411 analyzer (Roche Diagnostics) respectively, at the Canterbury Health Laboratories. The remaining plasma and serum samples will be analyzed at the Department of Human Nutrition, University of Otago, Dunedin Campus. For this, serum MMP-9 concentration will be measured using enzyme-linked immunosorbent assay (Human ELISA Kit, Invitrogen, Thermo Fisher Scientific), plasma glucose will be measured by enzymatic assays (Abbott C Series analyzer, Abbott Diagnostics), and alpha-1 acid glycoproteins will be measured using immunoturbidimetric assay (Cobas c311 analyzer, Roche Diagnostics).

#### Stool Samples

Once enrolled, participants submitted a stool sample using the provided OMNIgene.GUT|OM-200 (DNA Genotek) stool kit 24 hours before the clinic day at baseline and week 6. The samples were stored at room temperature until processing was done within a week. A total of 2 aliquots (2 g each) of stool samples were stored at –80°C until analysis.

DNA was extracted from the stool samples using the Macherey-Nagel NucleoSpin DNA stool kit per the manufacturer’s instructions. Only data relevant to analyzing the gut microbiome composition were extracted. Long-read Oxford Nanopore sequencing will be used for full-length 16S rRNA gene sequencing (~1500 bp) [54] to capture information from all 9 hypervariable 16S regions. Nanopore-generated sequence reads, which are re-base-called using “Super high accuracy base-calling” post run, will be passed through FastQC and then the standard EPI2ME amplicon workflow using the SILVA-138 database for taxonomic assignment.

#### Lepteridine Metabolites Acute Study

As a preliminary investigation into the postprandial absorption and excretion of selected mānuka honey-derived compounds, a randomized, crossover, acute study involving 6 healthy participants without symptoms of FD was conducted. Each participant attended 2 clinic visits, where they consumed 20 g of either of the Lepteridine-standardized mānuka honey formulations (containing 10 mg or 40 mg Lepteridine). After a 1-week washout, participants consumed the other formulation. The sequence in which they received the honey was randomly selected.

Blood and urine samples were collected before and after the participants consumed the assigned honey. To ensure they were hydrated, participants were asked to drink 250 mL of water every hour. Participants could not eat or drink any other food during the clinic except for the allocated study honey and water. Blood and urine samples were collected over 5 hours. A cannula was fixed by medically trained personnel to allow multiple blood sample collection at baseline (fasting samples) and at 0.5, 1, 2, and 5 hours after consuming the assigned honey. At each time point, 4 mL of blood was collected in a heparin and EDTA vacutainer. The blood was centrifuged at 3000 *g* for 10 minutes at 4 ℃, and aliquots were stored at –80 ℃. All urine voided during the 5-hour clinic was collected into sterile containers and stored at –80 ℃.

The analytical methods for measuring mānuka honey–derived compounds and metabolites will be based on a previous study that investigated the in vivo absorption and metabolism of Leptosperin over 3 hours [55], with amendments as required. Briefly, acidified urine will be extracted using solid-phase extraction (Strata-C18E cartridge, 3 mL, 500 mg, Phenomenex), which will be preconditioned with methanol and 0.1% acetic acid in water. After washing with 2 mL 0.1% acetic acid in water, metabolites will be eluted with 2 mL methanol and then analyzed by liquid chromatography with tandem mass spectrometry. For plasma, 20 µL of the sample will be extracted with 300 µL methanol, and the extract will be evaporated and reconstituted in 0.05% formic acid for liquid chromatography with tandem mass spectrometry. The analyses will be performed on an EXION high-performance liquid chromatography system fitted with a C18 column (Waters 1.7 µm ACQUITY UPLC BEH C18, 100 × 2.1 mm ID) attached to a SCIEX 6500+ Q-TRAP (AB SCIEX). Urine samples will be analyzed in precursor ion mode for m/z 211 (methyl syringate ion) while the plasma will be analyzed in multiple reaction monitoring modes. Biotransformer 3.0 [56] will be used to predict possible metabolites to extend the list of metabolites provided in Ishisaka et al [55]. The metabolites will be quantified using commercial standards where available.

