**Methods:**

This is a 3-arm, parallel, controlled, double-blind, randomized feasibility study. A total of 75 healthy adults with symptoms of functional dyspepsia (Rome IV criteria) and mild-to-moderate dyspepsia severity (Short Form Leeds Dyspepsia Questionnaire) were recruited between October 2022 and September 2023. Participants were randomized into one of three groups: (1) mānuka honey standardized to contain 10 mg/kg Lepteridine, (2) mānuka honey standardized to contain 40 mg/kg Lepteridine, or (3) honey maple flavored syrup control. After a 2-week lead-in period, participants consumed 10 g of allocated intervention twice daily for 6 weeks. Throughout the study, participants completed daily bowel movement diaries and validated weekly questionnaires about their gastrointestinal symptoms and quality of life. Stool samples and 3-day diet records were collected at baseline and the end of the intervention. Blood samples were collected at baseline, weeks 2 and 4, and at the end of the intervention. In addition, 6 healthy participants without symptoms of functional dyspepsia were recruited to undergo an acute 5-hour assessment for the appearance of Lepteridine and related metabolites in plasma and urine following consumption of Lepteridine-standardized mānuka honey. The study was approved by the Northern B Health and Disability Ethics Committee.

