### Objectives

The SOOTHE (Study of Mānuka Honey for Digestive Health) feasibility study aims to gather information required to design and undertake future clinical trials investigating the effect of Lepteridine-standardized mānuka honey on FD. The primary objective is to assess the effect of 6-week consumption of Lepteridine-standardized mānuka honey on symptom severity and quality of life in FD. This will be measured by changes in global Nepean Dyspepsia Index (NDI) scores from baseline to the end of the intervention. Data on recruitment time frame, strategies to improve recruitment, potential issues with adherence and attrition, and strategies to optimize adherence shall also be collected.

Secondary objectives include examining changes in Patient-Reported Outcome Measurement Information System (PROMIS gastrointestinal, anxiety, and depression) scores, immune parameters, and the gut microbiota composition between the Lepteridine-standardized mānuka honey and control groups. The study will also explore the pharmacokinetic profile of Lepteridine and other mānuka honey–derived metabolites in plasma and urine following acute consumption of Lepteridine-standardized mānuka honey.

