### Study Overview

This was a 3-arm, parallel, controlled, double-blind, randomized feasibility study in participants with FD with mild-to-moderate symptoms. The study duration was 10 weeks, consisting of a 2-week lead-in phase, a 6-week intervention phase, and a final 2-week follow-up phase (Figure 1). During the intervention phase, participants in 2 arms consumed 10 g of mānuka honey, standardized to contain either 10 mg or 40 mg/kg of Lepteridine twice daily. The third arm received 10 g of honey maple–flavored syrup twice daily as a placebo control.

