### Study Intervention

The active intervention for this feasibility study was monofloral mānuka honey standardized to contain either 10 or 40 mg/kg of natural Lepteridine. The concentration of naturally occurring compounds does not correlate with other known compounds found in mānuka honey, such as methylglyoxal. Lepteridine in mānuka honey is derived from the nectar of the mānuka. Naturally, it varies; therefore, to produce a mānuka honey product with standardized Lepteridine concentration, testing for the presence and quantity of Lepteridine in raw honey drums was undertaken, and the resulting drums were blended to achieve the desired concentration of Lepteridine in the final mānuka honey product [40]. The composition of the intervention products is shown in Table 1. Participants received the study products in unidentifiable sachets containing 10 g of Lepteridine-standardized mānuka honey or honey maple–flavored syrup solution. Participants took the assigned intervention before breakfast and dinner for 6 weeks. They were asked to avoid consuming any other honey during the study.

**Table 1 table1:** Composition of intervention product.

Nutrient	Mānuka honey^a^ per 100 g	Honey maple–flavored syrup^b^ per 100 g
Energy (kJ)	1370	1290
Carbohydrate (g)	80	76
Sugars (g)	78	76
Protein (g)	<1	<1
Fat (g)	<1	<1
Sodium (mg)	12	18

^a^Sourced from Comvita New Zealand.

^b^Sourced from New Zealand Sugar Company.

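### The acute substudy states Lepteridine amounts 50 times those implied by the product specification, and the only urine scan described cannot detect intact Lepteridine

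*Protocol article*

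**What the plan says.** **Amount consumed.** The section on the Lepteridine metabolites acute study describes a randomized crossover in 6 healthy participants who "consumed 20 g of either of the Lepteridine-standardized mānuka honey formulations (containing 10 mg or 40 mg Lepteridine"; after a 1-week washout they took the other formulation. The Study Intervention section defines the product as "monofloral mānuka honey standardized to contain either 10 or 40 mg/kg of natural Lepteridine". The Methods paragraph of the Abstract agrees, with one arm given "mānuka honey standardized to contain 10 mg/kg Lepteridine" and another "mānuka honey standardized to contain 40 mg/kg Lepteridine". The Study Overview is worded more loosely, "standardized to contain either 10 mg or 40 mg/kg of Lepteridine twice daily", with the per-kilogram unit attached only to the second figure.

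**Target in urine.** The Objectives section says "The study will also explore the pharmacokinetic profile of Lepteridine" and other honey-derived metabolites, in both plasma and urine. The Abstract likewise names Lepteridine in both fluids.

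**Urine assay.** The analytical paragraph of the acute-study section bases its methods on an earlier absorption study of a different compound, Leptosperin, to be amended where needed. It then says "Urine samples will be analyzed in precursor ion mode for m/z 211 (methyl syringate ion"), and gives multiple reaction monitoring as the mode for plasma. It describes no other detection mode for urine.

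**The concern.** The acute-study sentence gives a mass of honey and then what that mass contained, so a reader will take 10 mg and 40 mg as the amounts swallowed. That conflicts with the product specification. The section on protocol amendments says that nothing is known about absorption and metabolism of this honey in healthy people. The ingested amount is therefore a figure that later work may well take from this article.

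The second issue is separate. A precursor-ion scan reports only ions that break down to the selected fragment. The protocol's own label ties m/z 211 to methyl syringate, not to Lepteridine. If Lepteridine cannot yield that fragment, the urine half of the stated aim has no described measurement behind it, although all urine voided over 5 hours is collected and stored.

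**Working it through.** **1. Amount in 20 g**

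Inputs: 20 g = 0.020 kg (acute-study section); 10 and 40 mg/kg (Study Intervention, Abstract).

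Formula: amount = concentration × mass of honey.

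| Formulation | Implied by specification | Stated for 20 g | Ratio |
|---|---|---|---|
| Low | 10 × 0.020 = 0.2 mg | 10 mg | 10 / 0.2 = 50 |
| High | 40 × 0.020 = 0.8 mg | 40 mg | 40 / 0.8 = 50 |

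The stated figures are not reproduced. In reverse, 10 mg and 40 mg in 20 g would require 10 / 0.020 = 500 mg/kg and 40 / 0.020 = 2000 mg/kg. Equivalently, 10 mg at 10 mg/kg would need 1 kg of honey.

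**2. What the factor would and would not alter**

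The factor is the same for both formulations, so the ratio between them is unchanged: 0.8 / 0.2 = 40 / 10 = 4.

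Suppose the specification describes what was consumed, and someone divides by the printed milligrams. A true urinary recovery of 50% in the low formulation is 0.5 × 0.2 = 0.1 mg, and 0.1 / 10 = 1%. In the high formulation it is 0.5 × 0.8 = 0.4 mg, and 0.4 / 40 = 1%. Any dose-normalised quantity would shrink by the same 50-fold.

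**3. Whether m/z 211 can come from Lepteridine**

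The document prints no molecular mass, so the formula is derived from the name it gives, 3,6,7-trimethyllumazine: C9H10N4O2.

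- Monoisotopic mass: 9 × 12 + 10 × 1.00782503 + 4 × 14.0030740 + 2 × 15.9949146 = 206.08.
- Adding or removing a proton (1.00728): [M+H]+ = 207.09; [M−H]− = 205.07.
- Methyl syringate, C10H12O5: 10 × 12 + 12 × 1.00782503 + 5 × 15.9949146 = 212.07; [M−H]− = 211.06, which matches the protocol's label.

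A fragment of a singly charged ion cannot be heavier than the ion itself. Since 207.09 and 205.07 are both below 211, intact Lepteridine cannot appear in this scan in either polarity.

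**The case against.** The strongest reply has four parts.

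- **It is only a lost unit.** The sentence refers to the same standardized formulations, and the Study Overview also handles the unit loosely, so a dropped per-kilogram is plausible. That may explain the discrepancy but does not remove it: the text says what 20 g contained, and the loosely worded overview does not settle the matter.
- **No planned result depends on it.** A reader might infer that dose-normalised exposure and urinary recovery will be wrong. The document does not support this. It plans neither quantity, and the 50-fold error arises only if someone computes one from the printed milligrams. This part of the reply stands.
- **The scan harms less than it seems.** A reader might also infer that the acute substudy as a whole cannot answer its question. Plasma is read by multiple reaction monitoring and is untouched by the m/z 211 choice. In urine the scan would leave Lepteridine unmeasured; it would not produce a false value. This also stands.
- **The article only summarises the assay.** The description is introduced as brief, allows amendments, adds predicted metabolites and lists no plasma transitions. All true, and full assay detail may sit elsewhere. But the article does fix a urine mode, and the mode it fixes is unsuited to an analyte it names for urine. A general allowance for amendments does not replace that statement.

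**Conclusion.** Two errors stand. First, the acute-study section gives Lepteridine amounts 50 times those implied by the specification in the Abstract and Study Intervention section (10 and 40 mg against 0.2 and 0.8 mg in 20 g). This is a contradiction within the document, and the document alone does not establish which statement describes what was consumed. Second, the only urine detection mode described cannot detect intact Lepteridine, although the Abstract and Objectives name it as a urine target.

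The first result is plain arithmetic on printed figures. The second assumes the molecular formula derived from the chemical name and a singly charged intact ion; it says nothing about conjugates or other metabolites.

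Severity is minor to moderate. The substudy is exploratory and has six participants. The comparison between formulations, plasma measurement, the Nepean Dyspepsia Index outcome and the estimates meant to size future trials are all unaffected.

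**What to change.** **Amount.** Reconcile the acute-study section with the Abstract, Study Overview and Study Intervention section, using one unit throughout. Report each participant's ingested amount as the assayed concentration of the blend times the grams consumed, and use that figure in any dose-related result. This is a text correction plus a figure from product testing.

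**Urine.** Add a Lepteridine-specific multiple-reaction-monitoring transition for the stored urine, on the same instrument and alongside the m/z 211 scan. First check that the described solid-phase extraction retains and elutes Lepteridine, since the document does not show this. The cost is that recovery check and one further assay run on a small number of samples. If it cannot be done, withdraw the urinary Lepteridine objective and limit the urine aim to compounds that the scan can detect.

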### Data Analysis

#### Sample Size

The determinant of the sample size for this study was to enable the estimation of the SD and the potential effect size for the primary outcome. This estimation is crucial as it allows for sample size calculation in future trials, ensuring the study’s findings are robust and applicable. A sample size of 75 gives an estimated degree of freedom to calculate SDs, allowing reasonable precision.

#### Data Management

The study will generate quantitative and qualitative data, including questionnaires, laboratory data, clinically relevant information regarding symptoms, and face-to-face interviews on participants’ perceptions of the study protocol. Only data relevant to answering the research question will be collected. There was no anticipated harm during data collection beyond standard care and everyday life risks.

The data collected were in the form of electronic files, Microsoft Word documents, and a small number of paper-based questionnaires. Study data were collected and managed using the REDCap (Research Electronic Data Capture, Vanderbilt University) tool hosted at the University of Otago, Dunedin Campus. REDCap is a secure, web-based software platform designed to support data capture for research studies, providing (1) an intuitive interface for validated data capture, (2) audit trails for tracking data manipulation and export procedures, (3) automated export procedures for seamless data downloads to common statistical packages, and (4) procedures for data integration and interoperability with external sources [57,58]. It was only accessible to the researchers to contact participants for planned data collection. All participants were assigned a unique study identification number at the time of providing consent, which was recorded in REDCap and used instead of personal identifying information in all other data files. A formal data monitoring committee was not required as the intervention and control treatments in the study were considered sufficiently minimal risk. No harm was anticipated beyond the risks of standard care and everyday life. Data monitoring occurred through weekly meetings of the research team.

#### Data Collection and Storage

The researchers collecting data were trained in data collection and maintaining security and health-related confidentiality. Most of the data were collected electronically through the REDCap data capture system using unique identification. Participants who preferred paper-based data collection were accommodated. Paper-based and telephone-collected data were entered directly into the REDCap.

The data files were stored in Microsoft Excel for raw data and as data analysis files in R (version 4.3.2, R Foundation for Statistical Computing), Stata (version 18.0, StataCorp), or SPSS (version 29, IBM Corp). These data were only identified by the unique identification of the participant. Participants were identified by researchers only by their unique identification.

Raw data collected in hard copy were stored after electronic data entry as part of the case report form in a locked filing cabinet in the principal investigator’s (JM’s) office. Electronic data files generated in the study were stored on a password-secured University of Otago server or Otago OneDrive cloud storage. These files will be accessed as needed on password-protected computers of named investigators.

#### Statistical Analyses

All statistical analyses will be done using either R (version 4.3.2), Stata/SE version 18.0, or IBM SPSS version 29. The primary outcome analyses will use the intention-to-treat population (ITT) and per-protocol population. Secondary and exploratory analyses will be conducted with the ITT population. The ITT population will include all randomized participants who took at least 1 dose of the intervention. The per-protocol population will include those in ITT who had no major protocol violations, had all the study assessments required to analyze any outcome, and consumed at least 80% of their intervention product. Participants with missing data for a relevant outcome assessment will be imputed using the last observation carried forward.

The primary analysis will compare the overall NDI score changes for symptom severity and quality of life from baseline to week 6. Quality of life scores weighted by the participants’ perception of importance and unweighted scores will be examined. A general linear model that includes the randomized group as a fixed factor will be used (unadjusted results), and models adjusting for baseline values will also be presented. The residual plots from these analyses will be visually inspected, and if reasonable normality is not apparent, alternative generalized linear models will be undertaken.

For the secondary outcomes, changes in scores from baseline to the end of the intervention will be analyzed using appropriate statistical tests, depending on the data distribution. Descriptive statistics will be presented as frequencies, percentages, and mean (SD) for normally distributed parameters or medians (IQRs) for non-normally distributed parameters with a 95% CI and *P*≤.05 value to show statistical significance. Appropriate statistical techniques shall be used to mitigate any potential confounders and shall be reported in subsequent publications of this study. No formal hypothesis testing will be conducted on these variables.

Stool microbiome data will be analyzed using principal coordinate analysis and permutational multivariate ANOVA. Alpha-diversity and beta-diversity indices will be calculated. Differential abundance analysis of the microbiome abundance data (Analysis of Composition of Microbiomes with Bias Correction) [59] will be used to explore relationships between diet, metadata, diversity indices, and microbiome taxonomic traits. All analyses will be done in R with probability values adjusted for multiple comparisons using the Benjamini-Hochberg method [60] and data will be reported according to the reporting guidelines for human microbiome research (STORMS [Strengthening The Organizing and Reporting of Microbiome Studies]) [61].

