### Measurements and Their Timing

After enrollment, study clinic visits were undertaken at baseline, weeks 2, 4, and 6 (end of intervention). Currently, there is no information on the potential time course for which a treatment effect might be observed. Therefore, the multiple assessment time points enabled monitoring of potential symptom trends and identified optimal time points when any treatment effect can be observed. Table 2 shows when the study measurements were done. The information from this feasibility study will be used to determine the appropriate timing and selection of sensitive measurements for future trials.

**Table 2 table2:** Timing of study measurements.

Measurement	Lead-in week –2	Lead-in week –1	Baseline	Week 1	Week 2	Week 3	Week 4	Week 5	Week 6	Week 7	Follow-up week 8
Nepean Dyspepsia Index	✓		✓		✓		✓		✓		✓
Anthropometry^a^			✓		✓		✓		✓		
3-Day diet record		✓							✓		
Patient-Reported Outcomes Measurement Information System	✓	✓	✓	✓	✓	✓	✓	✓	✓	✓	✓
Daily bowel diary	✓	✓	✓	✓	✓	✓	✓	✓	✓	✓	✓
Blood samples			✓		✓		✓		✓		
Stool samples			✓						✓		

^a^Measured height, weight, and waist circumference at baseline and week 6; measured weight only at weeks 2 and 4.

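### Last observation carried forward is the only stated missing-data method; it can bias the week-6 intention-to-treat effects in either direction and forces zero change on missing week-6 stool data

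*Protocol article*

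**What the plan says.** The Statistical Analyses section of the protocol article first defines the analysis populations and then states, without restriction to any outcome: "Participants with missing data for a relevant outcome assessment will be imputed using the last observation carried forward". It names no other method for missing data.

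The rule operates in the intention-to-treat (ITT) set: "The ITT population will include all randomized participants who took at least 1 dose of the intervention". Anyone who starts the product and later drops out therefore stays in and is imputed. The rule also reaches beyond the primary outcome, because "Secondary and exploratory analyses will be conducted with the ITT population".

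The target is a single time point: "The primary analysis will compare the overall NDI score changes for symptom severity and quality of life from baseline to week 6". The model has randomized group as a fixed factor, and a baseline-adjusted version is also to be presented.

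Much more is collected. Table 2 has NDI at baseline and weeks 2, 4 and 6 (also at lead-in week -2 and follow-up week 8) and PROMIS every week. Stool is sampled only at baseline and week 6. Diet is recorded only in the week before baseline and in week 6.

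On purpose, Measurements and Their Timing says that "the multiple assessment time points enabled monitoring of potential symptom trends and identified optimal time points when any treatment effect can be observed". The Sample Size section says that the number of participants was chosen "to enable the estimation of the SD and the potential effect size for the primary outcome".

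**The concern.** LOCF assumes that a participant's score stays where it was at the last visit attended. The article says that the time course of any effect is unknown and gives this as the reason for repeated visits. The plan therefore has no basis for taking a baseline, week-2 or week-4 score as the week-6 score. If scores are still moving, the carried value understates the change in each arm, and by more in the arm that loses more people. The between-group difference can then shrink or grow. The linear model also counts each filled-in value as a real observation, so its standard errors ignore the uncertainty of imputation.

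This matters because the study is meant to supply the effect size and SD for the next trial. Required sample size varies with the inverse square of the effect, so an error in the effect is magnified when it is carried forward.

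Stool needs no assumption about time course. The only earlier value is the pre-treatment one, so the rule as written records no change.

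**Working it through.** **Plan's own figure.** There is none to reproduce. The article gives no SD or effect for NDI and no week-6 missingness by arm. The only attrition reported is 7 of 75 who withdrew before receiving any product. They fall outside the ITT set as defined, so LOCF does not touch them.

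**Inputs from the article.** Visits at weeks 0, 2, 4 and 6; 68 participants analysed in three arms; a minimum clinically important difference of 10 points for weighted NDI quality of life, used here only to scale the example.

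**Assumptions.** Improvement by week 6 of 15 points on control and 25 on honey, so the true difference is 10. Change is linear. Dropout is spread evenly after baseline, week 2 and week 4 and is unrelated to outcome.

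**Formula.** With share d missing at week 6, last seen at week t, and true change mu, the expected LOCF change in an arm is mu x [(1 - d) + d x t/6]. The mean of t over 0, 2 and 4 is 2, so this becomes mu x (1 - 2d/3).

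| Missing, control / honey | Control | Honey | LOCF difference |
|---|---|---|---|
| 10% / 10% | 15 x 0.933 = 14.0 | 25 x 0.933 = 23.3 | 9.3 |
| 20% / 20% | 15 x 0.867 = 13.0 | 25 x 0.867 = 21.7 | 8.7 |
| 5% / 20% | 15 x 0.967 = 14.5 | 25 x 0.867 = 21.7 | 7.2 |
| 20% / 5% | 15 x 0.867 = 13.0 | 25 x 0.967 = 24.2 | 11.2 |

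**Early plateau.** If the full response is reached by week 2, only those last seen at baseline (a third of the missing) are wrong, and the arm change is mu x (1 - d/3). The same four rows give 9.7, 9.3, 23.33 - 14.75 = 8.6, and 24.58 - 14.00 = 10.6. The bias is about half as large.

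**No true effect.** With equal missingness the bias is nil. With a change of 10 in both arms and 20% v 5% missing, the linear case gives a false difference of 10 x (2/3) x 0.15 = 1.0, and 1.5 if every dropout was last seen at baseline.

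**Comparison with a repeated-measures model.** A large-sample simulation used different assumptions: changes of 10 and 20 by week 6, SD 18 at each visit, within-person correlation 0.65, and dropout depending on the last observed score. The mixed model was fitted by maximum likelihood with unstructured covariance.

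| Missing, control / honey | True | LOCF | Mixed model |
|---|---|---|---|
| 12% / 11% | 10 | 9.2 | 10.0 |
| 23% / 21% | 10 | 8.5 | 10.0 |
| 6% / 21% | 10 | 6.9 | about 10.0 |
| 23% / 6% | 10 | 11.4 | 10.1 |
| 6% / 23% | 0 | -1.7 | about 0 |
| 23% / 6% | 0 | +1.7 | about 0 |

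Across these runs and the two no-effect runs with equal missingness, the SD of change under LOCF was 14.8 to 15.5, against a true 15.1. The effect is distorted, the SD hardly.

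**Consequence for the next trial.** Sample size scales with 1/effect squared. Planning on 8.7 (8.67 before rounding) instead of 10 multiplies it by (10/8.67)^2 = 1.33. Planning on 7.2 (7.17) multiplies it by 1.95, and on 11.2 (11.17) by 0.80.

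**Stool.** Here t = 0 for every missing week-6 sample, so the arm change is mu x (1 - d), and each imputed participant contributes exactly zero.

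**The case against.** The strongest reply is that the primary outcome is also analysed per protocol, and that set requires the assessments needed for the analysis. A primary analysis largely free of LOCF is therefore already planned. That stands, and it would be wrong to infer that every primary result depends on LOCF. But the per-protocol set also requires at least 80% product consumption and no major violations. It changes the population as well as the handling of missing data and cannot stand in for a sound ITT analysis.

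Second, the bias is conditional. A reader might infer that the week-6 effect will be biased by a known amount, or that the article predicts steady improvement. It supports neither: missingness after the first dose is not reported, the time course is said to be unknown, and the linear course and the 5% v 20% split are assumptions made here.

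Third, the bias is small beside sampling error. With an assumed SD of 20 and 68/3 = 22.7 per arm, the standard error of a difference is 20 x sqrt(2/22.7) = 5.9 and the 95% half-width about 12. Biases of 0.7 to 2.8 points are about 0.1 to 0.5 standard errors. That is fair, and the study was not powered for an effect. Even so, the bias is systematic and avoidable, and the estimate is what the study exists to deliver.

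Fourth, the article specifies no between-arm comparison of diet change, and its microbiome methods do not mention imputation. The zero-change point therefore rests on a literal reading of a general sentence, and for diet it applies only if change is analysed. A reader might also infer that the time-course aim has no analysis behind it. A journal article may leave that to the full plan, so it is not part of this point.

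**Conclusion.** The point holds in conditional form. LOCF is the only stated missing-data method and is not limited to any outcome. In the ITT analyses it can move the week-6 NDI and PROMIS effects either way, depending on how much is missing, when, and in which arm, and it counts imputed values as observed (this second effect was not quantified). For a true difference of 10 under linear change, the illustrated range is 7.2 to 11.2 with unequal loss and 8.7 to 9.3 with equal loss of 10% to 20%. It is nearer 10 if the response plateaus early or few values are missing, and the SD is little affected. The actual size cannot be derived from the article. For stool, read literally, the rule imputes exactly zero change. Data already scheduled for collection support a better method.

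**What to change.** Make the change before unblinding, by a dated amendment. The article keeps the team blinded until the primary analyses are complete, but data collection ended in December 2023 and analysis was under way by March 2024. If unblinding has already happened, report the new analysis alongside LOCF and label it post hoc.

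- NDI and PROMIS: replace LOCF with a mixed model for repeated measures with group, visit, group-by-visit and baseline. Use unstructured covariance, or a simpler structure for weekly PROMIS if the model does not converge. The week-6 contrast is primary.
- Stool, and diet if change is compared between arms: analyse participants with both records.
- LOCF: keep it, if at all, as a labelled sensitivity analysis.
- Report week-6 missingness by arm and last visit attended, so that readers can judge how much the choice matters.

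The cost is the amendment and some extra model fitting, with no new data. The mixed model assumes data are missing at random, so a sensitivity analysis to that assumption is advisable. Observed-pairs analysis loses participants without a week-6 sample and carries its own assumption about why samples are missing.
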